### Sample size

This study utilized a sample size calculation formula designed for comparing means between two independent groups. Our preliminary pilot-study data indicated a Simpson index of 0.8 in the OFS + AI group and 0.1 in the OFS + TAM group, with an effect size of *δ* = 0.7. Based on the literature-reported standard deviation of vaginal microbiota diversity (*σ* = 0.2), the effect size was calculated as d = δ/σ. The significance level was set at *α* = 0.05, with a statistical power of 1 - *β* = 0.8. The calculations suggested that 25 participants per group were necessary to detect a moderate effect size difference. Based on an annual cohort of 500 breast cancer patients, 20–30% (100–150 patients per year) are younger than 50 years. Over our planned 2-year recruitment period, we expect 200–300 eligible patients. Assuming a conservative recruitment rate of 40–50%, this allows us to successfully meet our target sample size of 110 participants (55 participants per group).

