**Methods:**

This single-center prospective cohort at Women’s Hospital, Zhejiang University School of Medicine, will enroll 110 premenopausal women (18–45 years) with hormone receptor-positive breast cancer, allocated to OFS + AI or OFS + TAM based on clinical regimens. Vaginal swabs collected at baseline and 1, 3, 6, 12 months undergo 16S rRNA sequencing (V3-V4 region) with DADA2-based ASV analysis via QIIME 2 for species-level resolution. Assessments include Vaginal Health Index (VHI), GSM symptoms (VAS for dryness, dyspareunia, burning), s, and urinary symptoms (ICIQ-SF). Primary outcomes: microbiome diversity (Simpson index) and Lactobacillus abundance. Secondary: VHI, VAS, urinary scores. Analyses use repeated measures ANOVA and generalized estimating equations; sample size accounts for medium effect (*d* = 0.8) and 10% attrition. Ethically approved and registered in Chinese Clinical Trial Registry.

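### The sample-size justification does not reproduce: the stated inputs give d = 3.5 (about 3 per group), 25 per group fits only d = 0.8, and neither leads to 110

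*Protocol article*

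**What the plan says.** The Sample size section names the method: "This study utilized a sample size calculation formula designed for comparing means between two independent groups". It reports pilot values, "Simpson index of 0.8 in the OFS + AI group and 0.1 in the OFS + TAM group", "with an effect size of *δ* = 0.7", takes sigma = 0.2 from the literature, and defines d as delta divided by sigma without printing the result. Alpha is 0.05 and power 0.8; the Statistical analysis section makes all tests two-sided. The stated result is "The calculations suggested that 25 participants per group were necessary to detect a moderate effect size difference".

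The section then turns to recruitment feasibility and ends at a "target sample size of 110 participants (55 participants per group"). No step from 25 to 55 is shown.

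The abstract (Methods) gives another basis: "sample size accounts for medium effect (*d* = 0.8) and 10% attrition". The value d = 0.8 and the 10% attrition are not mentioned in the Sample size section.

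**The concern.** The inputs, the formula and the result are all printed, and they disagree within one paragraph. The abstract adds a second standardised effect that cannot be obtained from the stated means and SD. The enrolment target is then about twice what the stated result plus the stated attrition would require.

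Comparing OFS + AI with OFS + TAM is one of the study's three aims. A reader who wants to know what difference 110 women can detect finds 0.7 Simpson units in one place and, by implication, 0.16 in another. Neither is the detectable difference for the number actually to be enrolled.

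**Working it through.** **Inputs.** Sample size section: means 0.8 and 0.1, delta = 0.7, sigma = 0.2, alpha 0.05, power 0.80, 25 per group, target 55 per group. Abstract: d = 0.8, attrition 10%. Statistical analysis section: two-sided tests.

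**Formula.** Normal approximation for two independent means: n per group = 2(1.960 + 0.8416)² / d² = 15.70 / d². Each result was checked with the noncentral-t solution for the two-sample t-test.

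**1. The plan's figure from its own inputs.** d = 0.7/0.2 = 3.5, so n = 15.70/12.25 = 1.3, rounded up to 2 per group. The t-test needs 2.67, so 3 per group (power 88.6% at n = 3). The stated 25 does not reproduce.

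**2. What 25 corresponds to.** With d = 0.8, n = 15.70/0.64 = 24.5, so 25 (t-test 25.5, so 26). The abstract's d therefore gives 25.
- At sigma = 0.2, d = 0.8 is a difference of 0.8 × 0.2 = 0.16, not 0.7.
- To keep delta = 0.7 with 25 per group, sigma would have to be 0.7 / (2.8016 × √(2/25)) = 0.88. The SD of an index confined to 0–1 cannot exceed 0.5.

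**3. The label.** By the usual 0.2/0.5/0.8 convention, 0.8 is large and 0.5 is medium. For d = 0.5, n = 15.70/0.25 = 62.8, so 63 (t-test 64) per group. With 25 per group the t-test power for d = 0.5 is 41%.

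**4. From 25 to 110.** Attrition: 25/(1 − 0.10) = 27.8, so 28 per group and 56 in total. Starting from the t-test's 26 gives 29 per group and 58 in total. The feasibility figures (200–300 eligible, 40–50% recruited) give 80 to 150 women. That range contains 110 but does not derive it.

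**5. Power at the planned size (t-test, two-sided 0.05).**

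| n per group | d = 0.8 | d = 0.5 |
|---|---|---|
| 55 | 98.6% | 74% |
| 49 (55 less 10%, rounded down) | 97.5% | 69% |

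**6. Detectable d at 80% power.** Approximately (z for alpha + 0.8416) × √(1/n₁ + 1/n₂). With 49 per group at alpha 0.05: 2.8016 × √(2/49) = 0.566 (t-test 0.572), or 0.572 × 0.2 = 0.11 Simpson units. At alpha 0.025 (Bonferroni for two primary outcomes): 3.083 × √(2/49) = 0.623 (t-test 0.631).

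Group sizes follow prescribing, so the split is not controlled. The t-test values below use illustrative splits; the unequal ones are assumptions.

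| Evaluable split | alpha 0.05 | alpha 0.025 |
|---|---|---|
| 49:49 | 0.572 | 0.631 |
| 60:39 | 0.582 | 0.642 |
| 66:33 | 0.603 | 0.666 |
| 72:27 | 0.639 | 0.705 |

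**The case against.** The strongest reply is that nothing is lost in practice. The planned 55 per group exceeds what either stated effect requires, and even an assumed 72:27 evaluable split keeps about 94% power for d = 0.8. That stands. A reader might infer from the failed arithmetic that the trial is too small, but the documents do not support that for any effect they state.

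The label can also be defended: the abstract attaches its own number to its medium effect, and the article does not cite the 0.2/0.5/0.8 convention. That reduces the label to a secondary point. It does not rescue the paragraph, because the Sample size section implies 3.5, which no usage would call moderate.

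Enrolling more than a calculated minimum is not an error, and an article may condense the route to its target. That is fair as far as it goes. But the abstract says the sample size accounts for 10% attrition, and that step gives 56, not 110.

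Three further inferences should be resisted:
- **That 110 is an inflated total (50 × 1.1 = 55) reused per group.** This is a guess; other undocumented routes also land near 55.
- **That 0.7 misstates what the study needs to find.** The article attributes the means to pilot data that are not shown, so this cannot be judged.
- **That a null result could not be interpreted.** It would be read from its estimate and confidence interval, not from the planning paragraph.

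Finally, a single replacement figure of d = 0.57 would itself mislead. The plan uses inverse probability weighting as the primary balancing approach, has two primary outcomes, and allows Bonferroni correction where appropriate. This objection is accepted and shapes the fix.

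**Conclusion.** The point holds as an error in the published justification, not as a shortage of patients. The stated means and SD give d = 3.5 and about 3 per group. The stated 25 belongs to d = 0.8, which contradicts those inputs and is conventionally a large effect. No stated input yields 55 per group or 110. As a result, no valid detectable difference is given for the number to be enrolled.

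The replacement values rest on assumptions: SD 0.2 from the article, 10% attrition, 80% power, and an unweighted two-sample t-test on one outcome at one time point. On that basis they are best-case figures: d of about 0.57 at alpha 0.05 and 0.63 at alpha 0.025. Variance lost to weighting and an uneven split raise them. If weighting left 80% of the effective sample (an assumption), they would be about 0.64 and 0.70. Gains from the repeated measurements could work in the other direction; the article gives no correlation from which to size them.

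**What to change.** Rewrite the Sample size section and the matching sentence of the abstract, keeping N at 110.

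1. Reconcile the pilot means, the SD and d between the two places, and say what each pilot value is. The pilot means should be explained or corrected, not silently deleted.
2. Remove the derivation of 25 per group from delta = 0.7, and the medium/moderate label.
3. State how 110 was chosen. If feasibility fixed it, say so.
4. State the detectable difference for 110 enrolled and about 49 evaluable per group: d of about 0.57 (0.11 Simpson units at SD 0.2) at alpha 0.05, and about 0.63 at alpha 0.025 if Bonferroni is applied to the two primary outcomes.
5. Label these as unadjusted best-case values for a single time point. Note that weighting and the uncontrolled split make them larger, and show a range of splits (for example 0.64 at alpha 0.05 for an assumed 72:27).

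The cost is wording only: no extra patients, visits or samples. The downside is a less favourable statement than the published one, because it gives up the claim that 25 per group suffice for a moderate effect. For the conventional medium effect of d = 0.5, the planned size gives 69% to 74% power.

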### Cohort classification

This study employed an observational prospective cohort design with non-randomized grouping based on real-world clinical practice. Patients were categorized into two groups according to the endocrine therapy regimen prescribed by their treating clinicians, taking into account individual disease characteristics, age, prior treatment history, and personalized clinical needs. The prescription of OFS + AI versus OFS + TAM is determined by the treating oncologist in accordance NCCN (3) based on clinicopathological risk factors. In brief: (1) OFS + AI is preferred for patients at high risk of recurrenceor those with contraindications to tamoxifen; (2) OFS + TAM is considered for patients with intermediate risk or those who cannot tolerate AI; (3) Patient preference and comorbidities (e.g., baseline cardiovascular risk, endometrial abnormalities) are taken into account. Any patient using oral contraceptives or levonorgestrel-releasing IUDs is required to discontinue/remove them prior to enrollment, since hormone receptor-positive breast cancer is a contraindication for systemic or local hormonal contraceptives.

To assess and address potential confounding, comprehensive baseline data were collected, including demographic characteristics (age, BMI, educational level, marital status), clinicopathological features (tumor size, lymph node status, TNM stage, histological grade), immunohistochemical markers (ER, PR, HER2 expression status, Ki-67 index), treatment-related factors (surgical approach, chemotherapy history, radiotherapy history), and laboratory parameters (estrogen levels). Patients who received (neo) adjuvant chemotherapy are eligible for inclusion. By strictly enforcing the hormonal inclusion criteria (FSH < 40 IU/L and Estradiol >20 pg./mL), we ensure that even patients with prior chemotherapy exposure are in a biochemically confirmed premenopausal state at baseline. For these patients, baseline sampling and assessment are performed at least 4 weeks after the last chemotherapy dose and prior to the initiation of endocrinotherapy. Chemotherapy history (regimen, number of cycles, dates) is recorded as a potential confounder, and subgroup analyses stratified by chemotherapy exposure will be performed.

A propensity score for receiving OFS + AI versus OFS + TAM will be estimated using a multivariable logistic regression model incorporating key baseline covariates, including age, BMI, tumor stage, prior chemotherapy exposure, and baseline ovarian function. Inverse Probability of Treatment Weighting (IPTW) will be used as the primary approach to balance baseline characteristics between the two groups. Stabilized weights will be calculated, which are truncated at the 1st and 99th percentiles to mitigate the influence of extreme weights. Standardized mean differences (SMD) will be assessed to confirm covariate balance, with an SMD < 0.1 considered acceptable.

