### Primary outcome

This study identified vaginal microbial diversity and the relative abundance of Lactobacillus as the primary outcome measures. High-throughput sequencing of the 16S rRNA V3-V4 region was utilized, and bioinformatics analysis was conducted using the DADA2 pipeline via QIIME 2 to generate ASVs, enabling single-nucleotide resolution for quantitative assessment of alterations in vaginal microecological diversity. Species-level identification, particularly for Lactobacillus species, will be performed based on ASV taxonomic assignment. Simultaneously, the relative abundance of the Lactobacillus genus within the total bacterial community was analyzed to evaluate vaginal microecological homeostasis. Measurement time points were established at baseline, and at 1 month, 3 months, 6 months, and 12 months post-treatment, thereby creating a comprehensive longitudinal observation trajectory.

The collection of vaginal microbial samples followed a strictly standardized procedure: participants were instructed to abstain from sexual intercourse, vaginal medications, and douching for 48 h prior to sampling. Additionally, individuals who were menstruating were scheduled for sampling within a 3- to 7-day window following the cessation of menstruation to minimize interference from the menstrual cycle. During the sampling process, participants were positioned in the lithotomy position, and the cervix was fully exposed using a sterile vaginal speculum. A sterile cotton swab was rotated in the posterior vaginal fornix for a duration of 10 s, subsequently placed into a sterile tube containing DNA/RNA Shield preservative, temporarily stored at 4 °C, and then transferred to a – 80 °C ultra-low temperature freezer for long-term storage within 4 hours.

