### Statistical analysis

This study utilized both the full analysis set (FAS) and the per-protocol set (PPS) for statistical evaluation. The FAS will include all enrolled participants who receive at least one dose of treatment and provide baseline data, analyzed according to their assigned group to minimize selection bias. The PPS will comprise participants who complete the study per protocol, excluding those with major violations such as non-adherence to treatment or loss to follow-up exceeding predefined thresholds. All tests will be two-sided, with a significance level of *α* = 0.05. Descriptive statistics will summarize continuous variables as mean ± standard deviation for normally distributed data or as median (interquartile range) for skewed distributions. Categorical variables will be presented as frequencies and percentages.

Given the observational nature of this cohort study, baseline imbalances between groups will be assessed using standardized mean differences. If substantial imbalances are detected (standardized mean difference >0.1 for key covariates), propensity score matching will be applied to create balanced subgroups for comparative analyses, with propensity scores estimated via logistic regression incorporating variables such as age, BMI, tumor stage, hormone receptor status, and chemotherapy history.

Between-group comparisons will use independent samples t-tests or Mann–Whitney U tests for continuous variables, depending on data distribution and variance homogeneity. Chi-square or Fisher’s exact tests will be applied for categorical variables.

For longitudinal analyses, we plan to use linear mixed-effects models (LMM) for continuous clinical outcomes (e.g., GSM symptom scores) and generalized linear mixed models (GLMM) for microbiome features (e.g., relative abundance of key taxa). Therapy group, time point, and their interaction will be included as fixed effects to evaluate whether temporal trajectories differ by treatment type. Repeated measures ANOVA (RM-ANOVA) will be retained only as a secondary sensitivity analysis for complete-case datasets. If the proportion of missing data for a given outcome exceeds 10%, multiple imputation by chained equations (MICE) will be performed under the missing-at-random (MAR) assumption, with 20 imputed datasets and pooled estimates using Rubin’s rules.

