Multivariable analyses will incorporate multiple linear regression and mixed-effects models, adjusting for confounders such as age, body mass index (BMI), tumor stage, hormone receptor status, and chemotherapy history. Stepwise regression will select variables to evaluate the independent effects of endocrine therapy regimens on vaginal microbiota changes. To address multiple comparisons across primary and secondary outcomes, Bonferroni correction will be applied where appropriate. Pre-specified subgroup analyses will be conducted, stratified by factors such as chemotherapy history and baseline estrogen levels, to explore heterogeneity of effects. Sensitivity analyses will verify result robustness, and subgroup findings will be interpreted cautiously as exploratory. All statistical analyses were executed using SPSS version 26.0 and R version 4.0 software.

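### Baseline Lactobacillus abundance and Simpson index are measured but named in no adjustment set, so a residual baseline difference between the non-randomised groups could appear as, or hide, a regimen effect

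*Protocol article*

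**What the plan says.** The Cohort classification section describes an "observational prospective cohort design with non-randomized grouping based on real-world clinical practice"; the regimen follows recurrence risk, contraindications, comorbidity and preference. The Primary outcome section names "vaginal microbial diversity and the relative abundance of Lactobacillus as the primary outcome measures" and states: "Measurement time points were established at baseline, and at 1 month, 3 months, 6 months, and 12 months post-treatment". A pre-treatment value of each primary outcome is therefore planned for every woman.

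Covariates are named in four places:

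- Cohort classification, data collection: "To assess and address potential confounding, comprehensive baseline data were collected", followed by demographic, tumour, receptor, treatment and estrogen variables.
- Cohort classification, weighting (the primary balancing approach): "incorporating key baseline covariates, including age, BMI, tumor stage, prior chemotherapy exposure, and baseline ovarian function".
- Statistical analysis, propensity score matching: "incorporating variables such as age, BMI, tumor stage, hormone receptor status, and chemotherapy history".
- Statistical analysis, multivariable models: "adjusting for confounders such as age, body mass index (BMI), tumor stage, hormone receptor status, and chemotherapy history". Stepwise regression then selects variables.

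None of the four names a baseline microbiome measure. For the longitudinal models the Statistical analysis section says: "Therapy group, time point, and their interaction will be included as fixed effects to evaluate whether temporal trajectories differ by treatment type".

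**The concern.** An outcome's own starting value is often among the strongest predictors of its later value, and in a non-randomised comparison it is an obvious candidate confounder. Here it is collected, yet it appears in none of the named adjustment sets. Nothing exempts such a term from stepwise removal if it is added later.

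Relative abundance is bounded: a woman who starts with little Lactobacillus has little to lose. If the groups start at different levels, they may change by different amounts even when the two regimens act identically. The Discussion expects a larger Lactobacillus loss on OFS + AI. If the AI women start lower, the change comparison could hide that effect; if they start higher, it could create one. This bears directly on the regimen-comparison aim.

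**Working it through.** The plan gives no figure on this point to reproduce. It supplies 55 women per group and a Simpson SD of 0.2 (Sample size section) and two-sided alpha of 0.05 (Statistical analysis section). It gives neither of two further inputs, so both are assumed and varied:

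- D, the baseline gap between groups, in SD units, remaining after any weighting.
- rho, the correlation between the baseline and a follow-up value.

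**Step 1. Can balance be assumed?** With 55 per group the standard error of a standardised mean difference (SMD) is sqrt(2/55) = 0.191. With no systematic difference at all, the chance that the absolute SMD exceeds the plan's 0.1 limit is 2 × (1 − Φ(0.1/0.191)) = 0.60. This is sampling variation, not bias. It shows only that the plan's own limit would often be exceeded on an unlisted variable.

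**Step 2. Bias in a change comparison when follow-up depends on baseline.** Take no regimen effect and unit variances, with follow-up = rho × baseline + noise. The group difference in change is rho × D − D = −(1 − rho) × D, and its standard error is sqrt(2(1 − rho)) × sqrt(2/55).

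For rho = 0.5 and D = 0.3 the bias is −0.15 SD, or 0.15 × 0.2 = 0.030 Simpson units in size. The standard error is 0.191 and the ratio 0.79. Type I error is Φ(−1.96 + 0.79) + Φ(−1.96 − 0.79), about 0.12. Over the range (size of bias in Simpson units; type I error):

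| D | rho = 0.3 | rho = 0.5 | rho = 0.7 |
|---|---|---|---|
| 0.1 SD | 0.014; 0.061 | 0.010; 0.058 | 0.006; 0.055 |
| 0.3 SD | 0.042; 0.154 | 0.030; 0.123 | 0.018; 0.093 |
| 0.5 SD | 0.070; 0.342 | 0.050; 0.259 | 0.030; 0.174 |

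**Step 3. Simulation check, and the opposite case.** 4,000 runs per setting, 55 per group, rho = 0.5, no regimen effect. Entries are bias in SD units; type I error.

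| Data pattern | D | Change comparison | Adjusted for baseline |
|---|---|---|---|
| Follow-up depends on baseline | 0.3 | −0.152; 0.126 | 0.001; 0.048 |
| Follow-up depends on baseline | 0.5 | −0.245; 0.246 | 0.004; 0.047 |
| Group gap stable over time | 0.3 | 0.006; 0.053 | 0.154; 0.155 |
| Group gap stable over time | 0.5 | −0.002; 0.050 | 0.247; 0.297 |

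An unadjusted comparison of follow-up values alone is biased under both patterns: type I error is 0.124 and 0.260 under the first, and 0.351 and 0.739 under the second.

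The model is simplified: two time points, normal data, no weighting and no attrition. It shows direction and order of size and does not predict this study's error rate.

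**The case against.** **The lists are open.** All three adjustment lists are given by way of example, and an article condenses a fuller plan. That stands: nothing excludes the baseline microbiome. But the article commits to a primary weighting method, a truncation rule, a balance limit and named covariates, and omits the most direct baseline measures it has. Naming them is a specific change, not a request for routine detail.

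**The longitudinal model might be read as having only group, time and interaction.** The text does not say so. Those terms are to be included; elsewhere the plan adds confounders to mixed models and weights on a propensity score. Chemotherapy, an obvious route to a baseline difference, is in all three lists. The eligibility limits on vaginal infection, antibiotics, hormones and symptoms may also narrow any gap.

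**It might be inferred that the balance check cannot see a microbiome imbalance.** The text does not confine the check to the listed examples; it simply does not commit to including these two variables.

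**It might be inferred that groups starting unequal must show different trajectories.** They need not. With baseline as a modelled visit, group-by-time removes a stable difference. The bias arises only if change depends on the starting level.

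**A fixed false-positive rate might be attached to the plan.** One bounded-abundance illustration has 49 per group, half of the Lactobacillus-dominant women losing dominance on either regimen, and 60% against 80% dominant at baseline. A raw-change t-test then rejects a true null 18% of the time, and 33% at 50% against 80%. These imbalances are assumed to survive weighting, and no document figure supports them; at 65% against 75% the rate is 8%. Scale matters too: in a proxy for the planned model, the interaction test rejects 4.7% and 6.3% with a log link but 20% and 34% with a logit link in the first two settings. The article states no link.

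**Compulsory baseline adjustment can itself mislead.** This stands, and the stable-gap rows above show it. It is the reason to report both analyses.

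**Conclusion.** The point holds in a limited form. Both primary outcomes have baseline values, the groups are not randomised, and no named adjustment set includes those values. If change depends on the starting level, a baseline microbiome gap remaining after adjustment can appear as, or hide, a regimen effect.

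The size cannot be determined from the document. Under rho = 0.5, no true effect and 55 per group, type I error in a change comparison is about 0.12 at a 0.3 SD gap and about 0.25 at 0.5 SD, against about 0.05 with baseline adjustment. At a 0.1 SD gap the inflation is negligible. If the gap is stable over time, the ranking of the two analyses reverses. Because they can disagree, the role of the baseline value should be fixed before outcome data are seen. This is worth correcting; it does not show that the planned comparison is invalid.

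**What to change.** - In the Cohort classification section (weighting) and the Statistical analysis section (matching), name baseline Lactobacillus abundance and baseline Simpson index as propensity-score covariates, and list both in the SMD balance table.
- For each primary outcome, pre-specify an analysis of the 1-, 3-, 6- and 12-month values adjusted for that outcome's own baseline, and exempt this term from stepwise removal.
- Report the group-by-time (change from baseline) analysis beside it as a sensitivity analysis, and state which weights it uses. Weights that equalise the baseline means make the weighted difference in change equal to the weighted difference at follow-up. To probe a stable gap, this analysis therefore needs weights without the two microbiome terms.

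The cost is wording, using swabs already planned, plus one or two more terms in models for 110 women. The handling of women without a usable baseline swab must be stated. The statistical downside is that baseline adjustment is biased if the group difference is stable over time; reporting both analyses shows whether the conclusion depends on that choice.

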### Patient involvement

The inclusion criteria for the study are as follows: (1) Female participants aged between 18 and 45 years; (2) Histopathological confirmation of invasive breast carcinoma; (3) Positive status for hormone receptors, specifically estrogen receptor (ER) and/or progesterone receptor (PR); (4) Premenopausal status at diagnosis, characterized by baseline follicle-stimulating hormone levels below 40 IU/L and estradiol levels exceeding 20 pg./mL; (5) Scheduled to undergo ovarian function suppression in conjunction with endocrine therapy; (6) Absence of GSM-related symptoms prior to the initiation of treatment; (7) Provision of written informed consent by the participants.

Exclusion criteria included: (1) the presence of concurrent malignancies; (2) severe dysfunction of cardiac, hepatic, or renal systems; (3) pregnancy or lactation; (4) a history of vaginal infection; (5) the use of antibiotics or hormonal medications within the preceding 3 months; (6) an expected survival of less than 2 years [determined by the PREDICT tool^1^ or multidisciplinary team consensus]; (7) patients with psychiatric disorders or those who have been on active treatment with medications known to significantly alter sexual function (e.g., SSRIs, SNRIs); and (8) Patients with active high-risk HPV infections or abnormal cervical cytology requiring intervention.

This study employed a systematic recruitment strategy at Women’s Hospital, Zhejiang University School of Medicine, leveraging its role as a regional center for breast cancer care. Research coordinators reviewed pathology reports daily to identify newly diagnosed patients, conducting preliminary screenings based on age and demographics to compile a list of potential participants. Recruitment was timed post-diagnosis disclosure but pre-treatment planning to enhance receptivity, avoiding the day of diagnosis to reduce emotional burden.

The structured process included: (1) Initial clinician-led introduction during routine visits, with interested patients referred to the research team; (2) Face-to-face detailed explanations of study objectives, procedures, risks, and benefits by coordinators or nurses; (3) A minimum 24-h consideration period without pressure; (4) Signing of informed consent after addressing queries; and (5) Immediate baseline data collection and examinations. This approach aimed to minimize bias and ensure ethical enrollment of 110 participants over 6 months.

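### Weighting and SMD-triggered matching are both prescribed for the OFS + AI versus OFS + TAM comparison, unranked and with different propensity lists, so the regimen estimate is not fixed

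*Protocol article*

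**What the plan says.** Three places in the protocol article deal with confounding in the comparison of OFS + AI with OFS + TAM.

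- **Cohort classification.** "Inverse Probability of Treatment Weighting (IPTW) will be used as the primary approach to balance baseline characteristics between the two groups". The weights are stabilised and truncated at percentiles 1 and 99. The propensity model uses key baseline covariates "including age, BMI, tumor stage, prior chemotherapy exposure, and baseline ovarian function". Balance is then checked, "with an SMD < 0.1 considered acceptable", and no action is given if the check fails.
- **Statistical analysis, paragraph on baseline imbalance.** "If substantial imbalances are detected (standardized mean difference >0.1 for key covariates"), then "propensity score matching will be applied to create balanced subgroups for comparative analyses". This second propensity model uses "variables such as age, BMI, tumor stage, hormone receptor status, and chemotherapy history". Weighting is not mentioned here or anywhere else in the section.
- **Statistical analysis, paragraph on multivariable analyses.** Multiple linear regression and mixed models adjust for a similar list, and stepwise regression picks the variables used to judge the independent effect of the regimen on the microbiota.

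The groups are not randomised. Cohort classification says that the treating oncologist chooses the regimen, with recurrence risk as a leading consideration. Sample size plans 110 women, 55 per group.

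**The concern.** Comparing the two regimens is a stated aim, and allocation follows prognosis, so how confounding is handled largely decides what the comparison means. Weighting and matching are not interchangeable. Stabilised inverse probability weights normally estimate the average effect over the whole cohort. Matching estimates an effect in the women who find a match and drops the rest. The two can give different estimates on different numbers of women.

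One section gives weighting as the unconditional primary approach. Another directs matching for the comparative analyses once a balance statistic has been seen. An analyst could follow either, or the stepwise regression, and claim to have kept to the protocol.

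**Working it through.** **1. The two adjustment plans side by side**

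| | Cohort classification | Statistical analysis |
|---|---|---|
| Method | Weighting, called primary | Matching |
| Condition | None | Baseline SMD above 0.1 for key covariates |
| In both propensity lists | Age, BMI, stage, chemotherapy | Age, BMI, stage, chemotherapy |
| In one list only | Baseline ovarian function | Hormone receptor status |
| Usual target | Whole cohort | Matched subset |
| Ranking of the two | Weighting is primary; matching not mentioned | None; weighting not mentioned |

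The item missing from the second list matters because loss of oestrogen is the mechanism under study. The item added needs a definition. Inclusion criterion 3 (Patient involvement) requires ER and/or PR positivity, so receptor status coded positive or negative is the same for every woman and adjusts for nothing. ER/PR pattern or level can vary, and ER and PR expression are recorded at baseline.

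**2. How often the trigger would be met**

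The article gives no figure for this, so there is none to reproduce.

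Inputs: 55 per group (Sample size); threshold 0.1 (Statistical analysis); four covariates, namely those common to both lists. To isolate chance, assume no true imbalance.

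- SE of an SMD ≈ √(1/55 + 1/55) = √(2/55) = 0.191.
- P(|SMD| > 0.1) = 2 × [1 − Φ(0.1/0.191)] = 0.60 for one covariate.
- At least one of four, independent: 1 − (1 − 0.60)⁴ = 1 − 0.40⁴ = 0.974.
- All four, independent: 0.60⁴ = 0.13.

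The text does not say whether one covariate is enough or all must exceed 0.1. By chance alone the rule is therefore met with probability between about 13% and 97%, depending on an unstated reading.

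A check of the any-one reading by simulation (20,000 runs, 55 per group, five covariates of which two binary) gave 99% with uncorrelated covariates and 97% at correlation 0.8. The per-covariate rate was 61%. Unequal groups change little: for assumed splits of 70:40 and 80:30 the formula gives 61% and 64% per covariate.

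These figures describe exchangeable groups. Because prescribing follows recurrence risk, real differences in prognostic factors such as stage and chemotherapy are likely, which makes the trigger more likely to be met.

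**3. The third route**

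The stepwise step lets the data choose the adjustment set for the regimen effect. Settling weighting against matching would not by itself fix the estimate.

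**The case against.** The best defence is that only weighting is called primary, so matching can be read as secondary or as a fallback when weighting leaves residual imbalance. The label does give weighting some precedence. But the trigger is defined on baseline imbalance between groups, not on weighted balance; the matching sentence is as directive as the weighting sentence; and nothing calls matching a sensitivity analysis. Even as a fallback, the choice of method would depend on the data.

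Other points on that side stand:

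- An SMD describes the sample in hand, and chance imbalance also confounds in a non-randomised cohort. Frequent triggering is not an error in itself. The fault is that two methods are unranked once the trigger is met.
- The propensity lists share four of five items, and both are open-ended. The difference is small, but it concerns ovarian function.
- A reader might infer that the regimen comparison rests wholly on the propensity step. It does not, because covariate-adjusted regression and mixed models are also planned.
- A reader might infer that receptor status is useless. That holds only for positive/negative coding.
- A reader might try to price the loss from matching. With an assumed 70:40 split, 1:1 matching keeps at most 40 pairs, so at least 30 of 110 women (27%) are dropped, and the detectable standardised difference goes from 0.56 to 0.63. The documents do not support this as the size of the problem. They plan 55:55, where a 1:1 cap drops nobody before any caliper, and the comparison ignores that weighting also reduces effective sample size.

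**Conclusion.** The concern holds as a conflict within the current text. For one comparison the article prescribes weighting unconditionally, matching conditionally, and stepwise regression as well, without an order among them. The method, the target population and the N of the regimen estimate are left open.

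The conflict does not depend on the probabilities; they show only that it is likely to arise in practice. The 60% per covariate assumes 55 per group and no true imbalance. The 97% further assumes that any one of four covariates is enough and that they are independent.

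Two stronger readings are not supported. The text does not say that matching replaces weighting; it leaves the relation unstated. Nor can the trigger be said to fire almost always by chance without the any-one reading, which the article does not give.

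**What to change.** 1. In Cohort classification, keep weighting as the single primary method, with one closed propensity list that includes baseline ovarian function.
2. In Statistical analysis, delete the SMD-triggered matching rule. If matching is wanted, label it a sensitivity analysis. Report weighted SMDs as a diagnostic that does not switch the method.
3. State that the between-group comparisons in the linear and generalised linear mixed models use the stabilised weights with robust standard errors.
4. Replace stepwise selection for the regimen effect with a pre-specified covariate set that includes the baseline value of the outcome, which the visit schedule already collects.
5. If hormone receptor status stays in any model, define it as ER/PR pattern or level.

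This should be settled before any outcome is compared by regimen. It needs no new data. The cost is protocol wording, slightly more analysis code, and some loss of effective sample size from weighting.
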